#### Phase 4: Beta Test

After completing baseline assessments, eligible participants will be emailed an invite link to the intervention Facebook group. Participants will be given instructions on how to register on Facebook. Those who already have a Facebook account can either create a new user profile or use the existing one to join the group. The research staff will ensure that the participants enroll in the group within 24 hours of receiving the link. If participants experience technical difficulties, the staff will assist them. The smokefree.gov resources will also be mailed to the participants. This phase will expose participants to 30 days of moderator postings and obtain feedback to ensure the system works as intended. In addition, we will conduct a preliminary assessment of feasibility and intervention uptake (engagement) to facilitate any needed refinements prior to future randomized controlled trial (RCT) (Figure 3).

**Figure 3 figure3:**
[figure not shown]
Overview of the process to develop faith-based Facebook intervention prototype and beta test to help rural people quit smoking. CAB: community advisory board; CE: community engagement.

### Measures

#### Overview

For aim 2, the beta testing phase, we will use an internet-based survey to measure the following. The participants in this study will receive a survey via email through REDCap (Vanderbilt University). The survey will be open for 7 days, and participants will receive 2 reminders to complete it. The email address on file is required for this process.

#### Baseline Smoking Characteristics

We will assess the average number of cigarettes per day, the age when the person started smoking, pack-years of smoking, the number of days the person smoked in the past 30 days [53], readiness to quit using the contemplation ladder [54], the average number of quit attempts in the past 30 days, and other commercial tobacco and nicotine product use.

#### Baseline Sociodemographic Characteristics

Sociodemographic measures selected from the PhenX Toolkit assessed age, sex, gender, ethnicity, race, education, employment status, and marital status [55].

#### Study Recruitment and Retention

Recruitment feasibility measures include the number of potential participants screened, the number of eligible participants, and the number of enrolled participants from the eligibility pool. Additionally, study retention will be evaluated by determining the proportion of participants who complete postintervention assessments.

#### Treatment Satisfaction

The satisfaction with the Facebook intervention will be measured in three domains: (1) perceived ease of use, (2) usefulness, and (3) satisfaction by using the Usefulness, Satisfaction, and Ease of Use (USE) questionnaire. The scale contains 13 items and participants will rate these items on a 5-point Likert scale, ranging from 1 (strongly disagree) to 5 (strongly agree). We will examine the Facebook intervention engagement patterns using Facebook metrics and qualitatively explore common topics that emerged in participant postings [56]. Additionally, we will include open-ended questions to gather more detailed feedback from users.

#### Intervention Uptake or Engagement

In order to measure the adoption of our intervention, we will use Facebook’s objective engagement metrics such as views, reactions (such as likes and loves), comments, posts, and poll votes (where participants can make multiple selections). By calculating the total number of times participants engaged with the intervention, we can accurately assess its uptake.

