#### Beta Test

A Facebook group size of 10 was the minimum number for optimal engagement in previous studies [47,48]. Thus, we will beta test the Facebook group with an estimated purposeful sample of 15 individuals who currently smoke and attempt to ensure that the sample comprises diverse individuals from different sexes, races, and age groups with fair representation. A 1-page information sheet or flyer codeveloped with the core research team and CAB will be posted on the Mayo Clinic display board and emailed or mailed to the community partner organizations, including local church partners. Study staff will administer an initial set of screening questions over the phone to screen for eligibility.

The eligibility criteria for participation are (1) aged >18 years; (2) smoked at least 1 cigarette per day over the past 7-day period; (3) have access to the internet on a mobile phone, computer, or tablet; (4) willing to create a Facebook account and willing to participate in the Facebook intervention for 1 month; and (5) either self-identify as a person of Christian faith or recognize that study posts will include Christian faith-based content, including Bible verses. Ineligible individuals (positive for smoking but unwilling to engage with Facebook intervention) will receive EBCT referral information via postal mail (printed materials) or email. The material will include information on their state tobacco quitline. Participants will also receive information on the National Cancer Institute’s free population-level smokefree.gov website resources. The website, tailored to all readiness levels to quit smoking, includes a quitting guide, texting program, smartphone apps, online live chat, URL, and a toll-free number ([name]) for state quitlines [26].

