#### Phase 3: Prototype Development and Moderator Training

The Mayo Clinic Social Media Department will assist in creating a study-related Facebook page. The group will be private, hidden, and moderated to facilitate confidentiality. By this stage, the content library will be finalized, and additional postings, including Bible verses and images, will be added on an as-needed basis based on insights and feedback from CBPR processes. The moderators’ interactions with group members are critical for sparking conversation among the group members. As a result, we will choose moderators who have knowledge of the Christian faith and are familiar with Bible verses. Given that our research team includes pastors from local churches, they will be consulted on an ongoing basis by the moderators if any guidance is required. The moderators will receive comprehensive training to ensure they possess the knowledge and skills for effective group moderation. The training will cover the principles of moderation, including the best ways to engage participants, promote appropriate conversations, and redirect engagement [51,52]. They will also be trained to handle challenging situations that may arise in a web-based group. Additionally, the moderators will participate in didactic training to learn basic communication principles, such as active listening, MI, and cognitive behavioral therapy. The ultimate goal is group participant interaction and partaking. Therefore, moderators will be encouraged to help generate daily interaction among members and not just post the content daily. Moderators will post 1 selection from the intervention content library every 1-2 days. In order to stimulate engagement from participants, the moderators will reply to the posts with 1-2 prompt questions (included in the content library) directed at specific individuals and using MI techniques. They will check the group several times daily to engage with participants and address inappropriate content or misinformation.

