### Statistical Analysis

Aim 1 will have 2 CAB meetings and 1 CE studio session. Members will be asked to provide helpful feedback on the content's flow, understandability, and relevance. Detailed notes will be taken during these meetings, and an iterative, inductive content analysis approach will be used to identify themes. A total of 2 investigators will work together to code the responses, and a third investigator will resolve any disagreements until a consensus is reached. Aim 2 will summarize sample characteristics, social media usability measures, and most and least preferred concepts using descriptive statistics, including means, percentages, and frequencies. Open-ended responses will be summarized, and themes will be generated using content analysis as described in aim 1.

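### Uptake is measured by a total count of engagement events that includes passive views; this does not show how many of the 15 participants engaged or whether they did more than view

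*Protocol article*

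**What the plan says.** Under Intervention Uptake or Engagement, the protocol article says that adoption will be measured with Facebook's "objective engagement metrics such as views, reactions (such as likes and loves), comments, posts, and poll votes (where participants can make multiple selections". It then gives the rule: "By calculating the total number of times participants engaged with the intervention, we can accurately assess its uptake". It states no count of participants who engaged, no threshold for having engaged, and no separation of viewing from acting.

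Four other places bear on the point:
- Beta Test: the plan is to "beta test the Facebook group with an estimated purposeful sample of 15 individuals".
- Phase 4: "This phase will expose participants to 30 days of moderator postings". The same section gives the purpose as a preliminary look at feasibility and uptake, so that refinements can be made before a future randomised trial.
- Phase 3: "Moderators will post 1 selection from the intervention content library every 1-2 days". This section also makes interaction among group members the ultimate aim of moderation.
- Treatment Satisfaction: "We will examine the Facebook intervention engagement patterns using Facebook metrics", together with a qualitative look at the topics of participants' postings.

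The Statistical Analysis section plans Aim 2 summaries "using descriptive statistics, including means, percentages, and frequencies" for sample characteristics, usability measures and preferred concepts. It does not name engagement or uptake.

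**The concern.** Uptake is one of the two things that Aim 2 sets out to assess, the other being feasibility. The intervention is peer support, so the useful questions are how many members take part and whether they interact. A count of events answers neither directly. One or two heavy users can produce a large total in a group of 15, and so can views alone in a group where nobody writes, reacts or votes.

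The choice of what to refine is at stake. A quiet group with two enthusiasts and a group in which most members talk to each other call for different changes before the next trial, yet both could report the same figure. The article also claims that the total measures uptake accurately, which may lead readers of the results to take it as sufficient.

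**Working it through.** The article gives no numerical target or calculation for uptake, so there is no stated figure to reproduce. The check is whether clearly different groups can yield the same total.

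**Inputs from the article**
- Participants: 15 (Beta Test).
- Exposure: 30 days (Phase 4).
- Posting rate: one library post every 1 to 2 days (Phase 3), so 30/2 = 15 to 30/1 = 30 posts.

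**Assumptions, for illustration only**
- All event types are added with equal weight.
- In the views-only case, each person views each post once.
- The splits between participants are invented to show what a total can hide.

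**Three groups with the same total, 15 posts**

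| Group | Events per person | Total | Mean | Median | Share of top two |
|---|---|---|---|---|---|
| (a) All view each post, no other action | 15 views | 15 × 15 = 225 | 15 | 15 | 30/225 = 13% |
| (b) All take part | 10 views + 5 active | 15 × (10 + 5) = 225 | 15 | 15 | 30/225 = 13% |
| (c) Two heavy users | 2 at 106, 13 at 1 | 2 × 106 + 13 × 1 = 225 | 15 | 1 | 212/225 = 94% |

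The total and the mean are identical in all three. The median separates (c) from the others. Only a split of views from active engagements separates (a) from (b).

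**30 posts.** Views alone can reach 15 × 30 = 450. The same 450 arises if 13 people contribute one event each and two people together contribute 450 − 13 = 437, which is 437/450 = 97%.

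**A less extreme split.** Two people with 100 events each and 13 with 5 each give 2 × 100 + 13 × 5 = 265. The mean is 265/15 = 17.7, the median is 5, and the top two hold 200/265 = 75%. Ten people at 18 and five at 17 also give 180 + 85 = 265, with a median of 18.

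**What a participant-level measure would show.** Count the participants with at least one active engagement. In (c), assume that the two heavy users are active and that each single event among the other 13 is a view.
- (a): 0/15.
- (b): 15/15 = 100% (exact Clopper-Pearson 95% interval 78.2% to 100%).
- (c): 2/15 = 13% (1.7% to 40.5%).

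The intervals only indicate how little 15 people can pin down. The sample is purposeful, so they should not be read as population estimates.

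**The case against.** Much can be said for the plan, and several stronger readings of the point do not stand.

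- **Pooling.** A reader might infer that the plan adds all metrics, equally weighted, into one group sum. That is the natural reading but not a literal one: totals by metric or by participant would fit the same words. Totals by metric would remove the mixing of views with actions, but would still hide how engagement is spread over participants.
- **Poll votes.** A reader might infer that each selection in a poll counts as a separate engagement. The article says only that several selections are possible. How they are counted is left open.
- **Engagement patterns.** The sentence under Treatment Satisfaction is a partial safeguard, and the qualitative reading of postings would expose a silent group. However, it names no statistic and does not alter the uptake rule.
- **Skewed means.** A reader might object that the Statistical Analysis section relies on means of skewed counts. That section does not name engagement, and its list of statistics is open-ended and includes percentages and frequencies. It neither causes the problem nor cures it.
- **Posting rate.** A reader might infer that the twofold range in posting distorts the result. There is one group and no comparison to bias, and the number of posts will be known. It is context for reading a count and no more.
- **Consequence.** A reader might infer that the total could wrongly settle whether the next trial goes ahead. The article sets no uptake threshold, describes a pilot randomised trial as already being planned, and reads uptake beside recruitment, retention, questionnaire scores and open-ended feedback.
- **Detail left to an analysis plan.** Week-by-week tables and similar detail can properly wait for a document not shown here. The measure itself is different, because the article states it and asserts that it is accurate.

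**Conclusion.** The point holds in a limited form. The article measures uptake by a total of engagement events, across metrics that include views, and says that this is accurate. Neither a total nor a mean derived from it can separate broad from concentrated engagement. If the total mixes metrics, it cannot separate viewing from active participation either. With the article's own 15 participants and 15 posts, 225 events is compatible with anything from 0 to 15 actively engaged people.

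That range rests on equal-weight counting and invented splits. It shows what the measure cannot distinguish, not what is likely to happen. If totals are reported by metric, the loss of information on spread across participants remains. The study is a descriptive beta test with no hypothesis test and no go/no-go rule, so this is a modest improvement to make and not a flaw that undermines the study.

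**What to change.** Define uptake at participant level:

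1. **Main measure:** the number and percent of all enrolled participants with at least one active engagement, meaning a reaction, comment, post or poll vote, with one vote counted per poll per person. The article sets no threshold for active engagement, so the team should confirm this one before the beta test starts.
2. **Spread:** the median and range of active engagements per participant.
3. **Views:** reported separately.
4. **Context:** the number of moderator posts made over the 30 days.
5. **Total:** kept as a secondary figure, with the word claiming accuracy deleted.

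The cost is a change of wording and a little more data extraction, by group member, from the same Facebook data. A key linking Facebook profiles to study IDs is optional. If one is used, it should be held apart from the study dataset, because the Ethical Consideration section says that beta-test data will be deidentified.

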### Statistical Analysis

Aim 1 will have 2 CAB meetings and 1 CE studio session. Members will be asked to provide helpful feedback on the content's flow, understandability, and relevance. Detailed notes will be taken during these meetings, and an iterative, inductive content analysis approach will be used to identify themes. A total of 2 investigators will work together to code the responses, and a third investigator will resolve any disagreements until a consensus is reached. Aim 2 will summarize sample characteristics, social media usability measures, and most and least preferred concepts using descriptive statistics, including means, percentages, and frequencies. Open-ended responses will be summarized, and themes will be generated using content analysis as described in aim 1.

### Missing Values

Because assigning missing data as smoking is not necessarily a conservative approach [57], we will also explore multiple imputation methods [58,59] to classify lost to follow-up as cigarette smokers or nonsmokers and conduct sensitivity analyses as appropriate.

### Ethical Consideration

The study was deemed exempt by the Mayo Clinic Institutional Review Board (23-000837). The CAB members will receive a US $150 honorarium. CE studio community experts will receive US $50. The participants will receive US $25 for completing the baseline assessment and US $25 for the postintervention assessment. For the beta test phase, study data will be deidentified.

## Results

The results of this project will lead to the development of a faith-based smoking cessation content library. In addition, we are planning a pilot 2-arm parallel group, RCT, which will include evaluation of control (mailed materials and smokefree.gov information) versus Facebook intervention (information mailed to the control group plus Facebook intervention developed during this study) among diverse populations.

## Discussion

### Principal Findings

Our study focuses on collaborating with community stakeholders to co-design a faith-based, peer-supported Facebook-delivered intervention prototype to address smoking cessation among rural people who smoke. This study is essential to a self-maintaining smoking cessation program for the rural population. We believe that Facebook group moderation is an important component of this program to increase participant engagement and provide behavioral support and access to cessation treatment resources and service linkages when required. In addition, the supervised Facebook group may lead to better peer support among participants who can learn from each other’s experiences and share their smoking cessation journey.

No such Facebook group exists that uses faith-based support as a component and encouragement to use EBCTs such as quitlines and cessation pharmacotherapy. During the preliminary meetings, our community stakeholders have shown interest in being trained as moderators and ensuring the continuity of the proposed Facebook group so that the intervention is self-maintained within the community once the study is over.

### Limitations

Our sample is restricted to the Midwest population and stakeholders, which may limit the generalizability to other rural populations. However, this phase is focused on prototype development, and future pilot study steps will pave the way toward larger, more generalizable evaluations of digitally enhanced interventions. Our study will recruit individuals with access to the internet and smart devices to access Facebook, which may lead to selection bias. For future studies, investigators may consider providing a loaner digital device to participants with no digital access to eliminate this selection bias.

### Conclusions

Our study will provide preliminary steps, including possible challenges before the RCT for a faith-based, Facebook-delivered EBCT intervention for rural populations that smoke. Our study has a broader interest in faith-based stakeholders and potentially be self-maintainable within the community. This approach can potentially support rural communities by granting them access to community-based health care that is maintainable. Our study design has the capability to provide a tailored online intervention with fidelity. Furthermore, our study uses existing federal and state EBCTs, using available resources to aid in smoking cessation.

## Abbreviations

CAB: community advisory board
CBPR: community-based participatory research
CCaTS: Center for Clinical and Translational Science
CDC: Centers for Disease Control and Prevention
CE: community engagement
CHCR: Center for Health Equity and Community Engagement Research
EBCT: evidence-based smoking cessation treatment
ITHBC: Integrated Theory of Health Behavior Change
MI: motivational interviewing
RCT: randomized controlled trial
USE: Usefulness, Satisfaction, and Ease of Use
